### Additional study

A nested, questionnaire-based, qualitative study will be conducted to explore the participants' reason for enrolling in this randomized controlled trial, experiences of dry-eye, and perceived changes after either acupuncture or artificial tear drop treatment. A questionnaire with open-ended questions will be distributed to all participants at the first, fifth and ninth week. They will be encouraged to write their responses in a comfortable environment. At baseline, patients in both groups will be asked how dye eye affects their lives and why they participated in this trial. At the fifth week, they will be asked how they feel after acupuncture treatment (or artificial tear drop treatment) and how they feel about being provided acupuncture treatment (or artificial tear drop treatment). At the ninth week, they will be asked how dry eye currently affects their lives and whether there was any change in their daily lives after treatment (acupuncture or artificial tear drops). Completed questionnaires will be collected at the next visit. Data will be analysed by a systematic text condensation method using the patients' written responses.

Cost-effectiveness will be analysed using the OSDI scores and comparing the cost of acupuncture with artificial tear drops for the two groups during the four-week treatment period. Additionally, the cost of dry-eye and other treatments (including acupuncture) for all of the participants during the follow-up period will be recorded and analysed.

### Statistical analysis

Statistical analysis will be conducted on an intention-to-treat basis with a 95% confidence interval using the SAS statistical package (SAS^® ^Version 9.1, SAS institute. Inc., Cary, NC). Missing values of drop-out participants will be imputed by the last observation carried forward (LOCF) method. Baseline characteristics will be displayed as the mean ± SD for continuous data or n (%) for categorical data. Because patient expectations may affect the treatment outcome [28], patient expectations (reported on a nine-point Likert scale before assignment of intervention) will also be compared between the two groups.

For analysis of baseline characteristics, either two-sample t tests or Wilcoxon rank sum tests for continuous data and Chi-squared tests or Fisher's exact tests for categorical data will be conducted after the test for normality. ANCOVA (Analysis of Covariance) will be used to test whether outcome measures (OSDI score, TFBUT, Schimer test result, QOL, VAS for self-assessment of ocular discomfort) differ between conditions when controlling for baseline and other covariates (including sites). Also, repeated measure analysis of variance will be performed to show changes in trends.

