### Sample size

The results from a previous study were used to calculate the sample size [13]. The mean difference and standard deviation (SD) of OSDI after acupuncture treatment were 17.61 and 15.61, respectively. According to another clinical trial with artificial tear drop, the supposed mean and SD of the artificial tear group were 11.3 and 6.3, respectively [14]. A two-sided 5% significance level and 80% power were considered, and the following equation was used:

$$n=\frac{2\times {\left(z_{\alpha /2}+z_{\beta }\right)}^{2}\times \sigma^{2}}{\delta^{2}}$$

*z*_*α*/2 _= *z*_0.025 _= 1.96; *z*_1-*β *_= *z*_0.8 _= 0.84

Approximately 60 participants in each group were calculated to be required. Therefore, estimating a 20% dropout rate, 75 participants will be recruited into each group. Among the 3 participating centres, all located in Korea, approximately 50 participants will be assigned to each to ensure an even distribution.

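### LOCF is fixed as the rule for drop-outs and can bias the week-5 OSDI contrast, by an amount that depends on when and in which arm people leave

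*Protocol article*

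**What the plan says.** The Statistical analysis section of the protocol article sets the analysis population: "Statistical analysis will be conducted on an intention-to-treat basis with a 95% confidence interval". It then gives the missing-data rule: "Missing values of drop-out participants will be imputed by the last observation carried forward (LOCF) method". Outcomes are compared by ANCOVA adjusting for baseline and site. A second analysis follows: "Also, repeated measure analysis of variance will be performed to show changes in trends".

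The Sample size section gives the planning values. For acupuncture: "The mean difference and standard deviation (SD) of OSDI after acupuncture treatment were 17.61 and 15.61, respectively". For tears: "the supposed mean and SD of the artificial tear group were 11.3 and 6.3, respectively". It allows for losses as follows: "Therefore, estimating a 20% dropout rate, 75 participants will be recruited into each group".

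Under Study aims, the null hypothesis concerns OSDI change after four weeks of treatment, which is read at week 5. OSDI is collected at weeks 1, 3, 5, 9 and 13. Schirmer and TFBUT are collected at weeks 1, 5 and 13 only. The section on the tear-drop comparator permits any dry-eye treatment during follow-up.

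**The concern.** LOCF assumes that a person who leaves stays where they were last seen. Here both arms are planned to improve, so a score carried from baseline asserts no improvement, and one carried from week 3 asserts that improvement stopped there. For Schirmer and TFBUT there is no visit between baseline and week 5, so every loss before week 5 is carried at baseline.

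Under equal dropout this pulls the primary contrast towards zero. Under unequal dropout it penalises the arm that loses more people, so the result partly reflects who left. In follow-up, a score from week 5 or earlier is copied into weeks 9 and 13, when other treatments are allowed. The repeated-measures trend is then partly flat by construction. Carried values are also analysed as if they had been observed.

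**Working it through.** **Inputs from the Sample size section.** Acupuncture change m = 17.61, s = 15.61; tears m = 11.3, s = 6.3; two-sided 5% level; 80% power; about 60 per group needed; 20% dropout; 75 per group recruited.

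**The plan's own figure.** The difference is 17.61 − 11.3 = 6.31. The pooled SD is √[(15.61² + 6.3²)/2] = 11.90. Then n = 2 × (1.96 + 0.84)² × 11.90² / 6.31² ≈ 55.8, so 56 per group. The stated figure of about 60 is a little above this, which is conservative, and 60/0.8 = 75 reproduces exactly. Without imputation, power is 82.7% on 60 completers per group; with no dropout it is 90.1% on 75.

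**Assumptions, because the article does not give these values.** A fraction d of an arm leaves before week 5. A share f of those leave before week 3 and carry a change of 0. The rest carry a week-3 change of q × m, with SD q × s (scaled) or s (unscaled). Dropout is unrelated to outcome. The test is unadjusted, since the baseline correlation needed for the ANCOVA is not stated.

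**Formulas, per arm, SD scaled.**
- Mean M = (1 − d)m + d(1 − f)qm
- Variance V = [(1 − d) + d(1 − f)q²](s² + m²) − M²
- Contrast D = M(acupuncture) − M(tears); SE = √[(V₁ + V₂)/75]; power ≈ Φ(D/SE − 1.96)

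**Worked case: d = 20% in both arms, all before week 3 (f = 1).**
- Acupuncture: M = 0.8 × 17.61 = 14.088; V = 0.8 × (243.67 + 310.11) − 14.088² = 244.56
- Tears: M = 0.8 × 11.3 = 9.04; V = 0.8 × (39.69 + 127.69) − 9.04² = 52.18
- D = 5.05; SE = √(296.74/75) = 1.989; power = Φ(2.538 − 1.96) ≈ 72%

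**Equal 20% dropout, 75 per arm**

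| Share leaving before week 3 | Week-3 share of effect | Contrast | Power, SD scaled (unscaled) |
|---|---|---|---|
| All | any | 5.05 | 72% (72%) |
| Half | 50% | 5.36 | 79.5% (76.5%) |
| Half | 75% | 5.52 | 81% (79.5%) |
| Half | 100% | 5.68 | 82% (82%) |
| None | 50% | 5.68 | 86% (81%) |
| None | 75% | 5.99 | 89% (86%) |
| None | 100% | 6.31 | 90% (90%) |

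With the SD scaled, power falls below 80% once about 47% to 60% of the drop-outs leave before week 3. With the SD unscaled and week 3 at half the effect, a quarter leaving early already gives 79%. If all leave before week 3, power falls below 80% from about 12% dropout. If only half of the 20% are lost by week 5, even with all of them carrying baseline, the contrast is 0.9 × 6.31 = 5.68 and power about 82%.

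**Unequal dropout at the planned effects, all carrying baseline.** At 10% acupuncture and 30% tears: 0.9 × 17.61 − 0.7 × 11.3 = 7.94, which is inflated. At 30% and 10%: 0.7 × 17.61 − 0.9 × 11.3 = 2.16, with power about 20%.

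**No true difference (both arms improve by 11.3), week 3 at half the effect.** The false difference is 11.3 × (gap in dropout) × [1 − 0.5(1 − f)]. Rejection ranges cover either arm losing more.

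| Share leaving before week 3 | 10% v 30% | 15% v 25% |
|---|---|---|
| All | 2.26 points; 21–24% | 1.13 points; 9% |
| Half | 1.70 points; 14–16% | 0.85 points; 7% |
| None | 1.13 points; 9–10% | 0.57 points; 6% |

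At 20% in both arms the false difference is 0 and rejection is 5%.

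**The case against.** A reader might infer that LOCF will bring power below the planned 80%. The article does not support that as a certainty. LOCF keeps 75 per arm in the analysis, and many of the timing patterns above leave power at or above 80%. The 20% carries no time point and follow-up runs to week 13; those who leave after week 5 have an observed primary outcome that LOCF does not touch.

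A reader might also infer that unequal dropout is likely, since allocation is known to participants and one arm attends three needling sessions a week while the other uses drops at home. That makes imbalance plausible, but the article gives no arm-specific rate and plans the same 75 for each group. The 21% to 24% rejection needs both a threefold imbalance and every drop-out leaving before week 3.

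The follow-up distortion lies outside the primary contrast, and free use of other treatments makes weeks 9 and 13 hard to read under any method. Absence of a not-at-random sensitivity analysis is no finding either, because an unshown analysis plan may contain one.

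These objections limit the size and certainty of the problem. They do not remove it: LOCF is a stated rule rather than an omitted detail, and the article offers no reason to expect scores to stay still after dropout in arms planned to improve. The higher power under late dropout also depends on counting week-3 scores as week-5 outcomes.

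**Conclusion.** The point stands in conditional form. LOCF as the stated rule can bias the week-5 OSDI contrast. Equal dropout shrinks it, except where the week-3 change already equals the week-5 change. Unequal dropout can shift it either way and raise the type I error above 5%. The figures rest on the plan's means and SDs and on assumed timing, arm split and week-3 effect, so they show a range and are not a forecast. The distortion of weeks 9 and 13, and the carrying of baseline for Schirmer and TFBUT, follow directly from the visit schedule for anyone who leaves before those visits. This should be fixed before analysis; it does not by itself invalidate the design.

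**What to change.** Replace LOCF as the primary method with a likelihood-based mixed model for repeated measures on all observed OSDI visits. Include baseline OSDI, site, group, visit and group-by-visit, and name the week-5 group contrast as primary. Use the same model for the trend analysis in place of the repeated-measures ANOVA on filled-in data. Keep LOCF only as a sensitivity analysis.

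The cost is a change of wording and a slightly more complex analysis, with no extra participants or visits. The model relies on a missing-at-random assumption that the data cannot verify. As a guide to power, 60 observed per arm at the full 6.31-point difference gives about 83% in the unadjusted calculation, so the planned 80% is kept even if the whole 20% is lost before week 5, provided that assumption holds.

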### Study aims

The primary aim of this study is to determine the effectiveness of acupuncture treatment for dry eye. The null hypothesis is that changes in the ocular surface disease index (OSDI) are equal in both the acupuncture treatment group and the artificial tear drop group after 4 weeks of treatment.

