### Eligibility Criteria

We will include patients who have dry eye symptoms (e.g. ocular itching, foreign body sensation, burning, pain and dryness, visual disturbance, ocular redness and sensation of tearing in a single eye or in both eyes) of at least moderate severity (i.e. tear film break-up time [TFBUT] is below 10 seconds and Schirmer I test result is below 10 mm/5 minutes) [12]. Participants will be excluded if they have prominent pathological changes of the eyelid, eyelashes, eyeball or eye accessories due to acute infection; Stevens-Johnson syndrome; Vitamin A deficiency; external injuries; a history of surgical operation related to the eye in the previous three months; punctual occlusion; sequelae of facial palsy; usage of anti-inflammatory eye drops within two weeks before entry; pregnancy; or usage of herbal medicine, acupuncture, or cupping therapy within 1 month before entry. In addition, usage of contact lenses within 2 weeks before entry, and throughout the study, is prohibited. The eligibility were assessed by physicians and ophthalmologists [13].

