### Randomisation and Allocation Concealment

Random numbers will be generated by a computerised random-number generator through the block-randomisation method of the SAS package (Version 9.1.3; SAS institute Inc.) for sequence generation. A clinical research associate (CRA) will make opaque blinded assignment envelopes (with consecutive numbers) and deliver them to each participating centre. The block size and treatment-assignment table will not be available to the researchers until the end of the study.

Random allocation will be performed at the second visit for each participant. According to the number assigned to a participant, the corresponding envelope will be opened in front of the participant to reveal treatment. Either acupuncture or artificial tear drop treatments will be initiated at the second visit after the assignment. Objective outcomes (i.e. Schimer test and TFBUT) will be examined by different ophthalmologists, while self-reported outcomes (e.g. OSDI, visual analogue scale (VAS), quality of life (QOL), and general assessment) will be assessed by different outcome assessors.

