### Primary outcome measurement

The OSDI is a questionnaire that consists of twelve questions about ocular irritation and the effect of dry eye on vision [20]. It will be assessed at the first, third, fifth, ninth and thirteenth week. For every question, participants will provide a score between zero and four, where zero equals "none of the time" and four equals "all of the time". OSDI scores will be calculated according to the following formula: OSDI = [(sum of scores for all questions answered)*100]/[(total number of questions answered)*4]. The Korean version of OSDI has not been validated yet. However, there is no available tool for evaluating dry eye that validation test for translation was finished about in Korea. So we will use the Korean version of OSDI which has been widely used for practice and research since 2006, in spite of these limitations [13,21,22].

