### Secondary outcome measurement

A VAS for self assessment of ocular discomfort will be reported by participants. Ocular symptoms related to dry eye (e.g. ocular itching, foreign body sensation, burning, pain and dryness, blurred vision, sensation of photophobia, ocular redness, and sensations of tearing) will all be reported using a standard 100-mm VAS scale.

QOL questionnaire of the Measure Yourself Medical Outcome Profile-2 (MYMOP-2) will be used to assess dry-eye-related QOL [23,24]. A seven-point Likert scale (from zero-'Excellent' to six-'Worst') will be used. The questionnaire is: "During last week, how would you express your quality of life related to dry eye overall?" The VAS and questionnaire for QOL will be assessed at the first, third, fifth, ninth and thirteenth week.

The Schirmer I test (with anaesthesia) is a diagnostic method to measure the basic quantity of tear secretion [25]. After application of local anaesthesia, Schirmer test paper (Color BarTM Eagle Vision, USA) will be placed in the lateral third of the lower eyelid for five minutes while the participants' eyes are closed.

Tear film break-up time (TFBUT) is a method for observing tear film stability [26,27]. Sodium fluorescein (2.5%) will be applied to both eyes, and the tear break-up time (i.e. the interval between the last complete blink and the first appearance of a dry spot or disruption in the tear film) will be measured. Both the Schimer test and TFBUT will be assessed at the first, fifth and thirteenth week.

Acupuncture practitioners and participants will evaluate general improvement of dry eye-related symptoms using a five-grade scale: excellent, good, fair, poor and aggravation. This will be assessed after the end of the treatment period (the fifth week).

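### The secondary repeated-measures ANOVA names no baseline adjustment; if week 1 is entered as a response, it loses power and its time effect is hard to read, while the baseline-adjusted primary comparison is unaffected

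*Protocol article*

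**What the plan says.** The Statistical analysis section of the protocol article names two methods for the continuous outcomes. The first is ANCOVA, to test whether OSDI, TFBUT, Schirmer, QOL and VAS "differ between conditions when controlling for baseline and other covariates (including sites"). The second is one sentence: "Also, repeated measure analysis of variance will be performed to show changes in trends". It does not say whether the week-1 value is a response or a covariate, which effect is tested, what covariance is assumed, or whether a sphericity correction applies.

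The visits are set under the outcome headings. For OSDI: "It will be assessed at the first, third, fifth, ninth and thirteenth week". For the patient-reported secondary outcomes: "The VAS and questionnaire for QOL will be assessed at the first, third, fifth, ninth and thirteenth week". For the objective tests: "Both the Schimer test and TFBUT will be assessed at the first, fifth and thirteenth week". Under Randomisation and Allocation Concealment, "Either acupuncture or artificial tear drop treatments will be initiated at the second visit after the assignment", so the first-week value is read here as pre-treatment. Entry requires "at least moderate severity (i.e. tear film break-up time [TFBUT] is below 10 seconds and Schirmer I test result is below 10 mm/5 minutes"); there is no OSDI threshold. The null hypothesis under Study aims is that OSDI changes "are equal in both the acupuncture treatment group and the artificial tear drop group after 4 weeks of treatment".

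**The concern.** The two adjacent sentences differ: one adjusts for baseline and the other names no adjustment. In the usual layout of a repeated-measures ANOVA, every scheduled visit is a response level, including the one before treatment. Three things then follow.

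- The arm main effect averages in a visit at which the arms cannot differ through treatment. It also keeps the between-person variance that a baseline covariate would remove.
- The arm-by-time F test assumes sphericity, although the visits are 2, 2, 4 and 4 weeks apart.
- The time effect, which is the most literal reading of a change in trend, has no untreated reference. Two of the outcomes were also selected to be low at entry.

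At stake is how the secondary time-course analysis will be read. One ANOVA table could show no arm effect, a significant interaction and a strong time effect, and the article does not say which of these answers the question.

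**Working it through.** The document gives no figure for this analysis, so there is none of its own to reproduce.

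**Inputs from the article.** 60 analysable per arm and 75 recruited (60 / (1 − 0.20) = 75); 5 visits for OSDI, VAS and QOL; 3 visits for TFBUT and Schirmer; two-sided 5% level.

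**Inputs assumed, because the article gives none.** A constant standardised effect d = 0.4 at every post-baseline visit, unit variance, and the between-visit correlations stated below. Steps 1 to 4 take week 1 as a response in the repeated-measures ANOVA.

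**1. Dilution of the arm main effect.** With T visits, no effect at the first and d at the others, the averaged arm difference is d × (T − 1)/T.
- T = 5: 4/5 = 0.80, so 0.40 becomes 0.32.
- T = 3: 2/3 = 0.67, so 0.40 becomes 0.267.

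**2. Power in closed form (75 per arm, equal correlation r = 0.5).**

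Variance of a participant's mean over all visits: [1 + (T − 1)r]/T. Variance of the post-baseline mean after baseline adjustment: [1 + (T − 2)r]/(T − 1) − r². The standard error of the arm difference is √(2 × variance / 75), and power is Φ(effect/SE − 1.96). For arm-by-time, the noncentrality is (75/2) × d² × [(T − 1)/T] / (1 − r), referred to F with T − 1 and 148(T − 1) degrees of freedom.

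| | 5 visits | 3 visits |
|---|---|---|
| Main effect: variance | (1 + 2)/5 = 0.600 | (1 + 1)/3 = 0.667 |
| Main effect: effect/SE | 0.32/0.1265 = 2.53 | 0.267/0.1333 = 2.00 |
| Main effect: power | 72% | 52% |
| Arm-by-time: noncentrality | 37.5 × 0.16 × 0.8/0.5 = 9.6 | 37.5 × 0.16 × 0.667/0.5 = 8.0 |
| Arm-by-time: power | 69% | 71% |
| Baseline-adjusted: variance | 0.625 − 0.25 = 0.375 | 0.75 − 0.25 = 0.50 |
| Baseline-adjusted: effect/SE | 0.40/0.100 = 4.00 | 0.40/0.1155 = 3.46 |
| Baseline-adjusted: power | 98% | 93% |

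**3. Power with decaying correlation (simulation).** For 60 to 75 per arm, d = 0.4 and correlation of 0.80 to 0.95 per week, over both visit schedules:
- arm main effect: 38–81%;
- arm-by-time with Greenhouse-Geisser correction: 36–89%;
- baseline-adjusted post-baseline comparison: 86–99%.

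A repeat run for this write-up agreed within about two percentage points (37–81%, 38–91% and 85–99.8%).

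The loss varies widely with the assumptions. With 60 per arm, the change SDs under Sample size (15.61 and 6.3), an assumed baseline SD of 20 and a sustained difference of 17.61 − 11.3 = 6.31 points, the main effect had 24–26% power and week-5 ANCOVA 81–83%. In that setting the arm-by-time test reached 85%. So arm-by-time is not always weaker than an ANCOVA at a single visit. The comparator that beats it in steps 2 and 3 is the adjusted analysis of all post-baseline visits.

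**4. Type I error of the arm-by-time test (simulation, 75 per arm).**
- Equal correlation: about 5%.
- Correlation decaying with time (4-week correlation 0.3 to 0.9), uncorrected: 5.6–8.5% with 5 visits and 5.0–6.5% with 3.
- At 0.80 to 0.95 per week (60 to 75 per arm): 4.6–7.5% uncorrected and 4.3–5.3% with Greenhouse-Geisser.

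**5. Regression to the mean.** If the qualifying measurement also serves as the week-1 value, selecting the lowest share p of a normal variable gives an expected rise at retest of (1 − r) × φ(z_p)/p SD. Example with p = 0.5, r = 0.5: 0.5 × 0.399/0.5 = 0.40 SD. Over p = 0.25 to 0.75 and r = 0.3 to 0.9, the rise is 0.04 to 0.89 SD. It applies to the two outcomes with an entry cut-off and is equal on average in the randomised arms.

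**The case against.** The strongest reply is that this is a supplementary analysis described in one sentence of a condensed article. How week 1 enters, the covariance and any correction are details that a fuller document may settle. The between-arm question belongs to the ANCOVA, which does adjust for baseline, and the ANCOVA sentence is not limited to week 5. An analysis of trends would naturally be read from the arm-by-time term, which the 4/5 and 2/3 factors do not touch.

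Most of this stands. It makes the point conditional and limits it to a secondary analysis. What remains is that the article names a method which, in its usual form, uses the baseline less well than the method one sentence earlier, and that the arm-by-time test is also weaker than the adjusted alternative under the assumptions of steps 2 and 3.

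A reader might go further in three ways that the document does not support.

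- That the trend test will exceed 5%. This needs an uncorrected univariate F and departure from sphericity; omitting baseline adjustment does not cause it.
- That regression to the mean threatens the treatment comparison or the primary outcome. It falls on both arms alike, and OSDI has no entry cut-off.
- That rises over time will be presented as efficacy. The article does not say so.

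**Conclusion.** The point holds in conditional form and at low severity. If week 1 is a response, the dilution to 4/5 or 2/3 of a sustained effect is exact arithmetic. The power loss is real but depends on assumed correlations and on an effect that persists through week 13. That persistence is uncertain, because the article allows any dry-eye treatment during follow-up. The possible error rate of about 5–8% goes away with a Greenhouse-Geisser correction. Regression to the mean affects only the pooled time effects of TFBUT and Schirmer.

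It would be wrong to conclude that the trial's main result is at risk: the hypothesis concerns OSDI change after 4 weeks, and the baseline-adjusted ANCOVA that tests it does not depend on this analysis. The change is worth making because it is cheap and gives a more precise time-course analysis from data already collected.

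**What to change.** Replace the repeated-measures ANOVA, as a secondary analysis only, with a mixed model for the post-baseline visits. Take the baseline value and site as covariates; arm, visit and arm-by-visit as fixed effects; and an unstructured covariance across visits. Report the adjusted arm difference with its 95% confidence interval at each visit. State that time effects and within-arm changes are descriptive and support no claim of effect.

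The cost is a change of wording and a few lines of code in the SAS package already named; no new data are needed. There are two downsides. Within-arm trend p-values are no longer reported. The model also uses observed data by likelihood, so it departs from the article's LOCF rule; the plan should say that LOCF does not apply to this secondary model. The primary ANCOVA need not change.
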